#### Randomization and stratification

Patients will be centrally randomized to receive regorafenib or placebo, in a double blind fashion, and in a 1:1 ratio respectively. Four strata will be identified: leiomyosarcoma (50 patients), liposarcoma (50 patients), other sarcoma (50 patients) and synovial sarcoma (26 patients). A permuted blocks randomization technique will be used for treatment allocation. Within the 4 strata, stratification factors will be: prior exposure to pazopanib (yes/no) and countries.

#### Analysis sets

The following patient populations will be considered in the final analyses.Intention-to-treat population: All randomized patients will be analyzed in the arm they were allocated by randomization.Per protocol population: All patients who are eligible and have started their allocated treatment (at least one dose of the study drug)Safety population: All patients who have started treatment (at least one dose of the study drug)

A patient will be considered to be eligible if he/she did not have any major deviations from the patient entry criteria listed in chapter 3 of the protocol. Eligibility will be assessed by the Study Coordinator based on the review of each patient file.

The primary analysis will be conducted on the Intention-to-treat population.

#### Statistical analysis

Progression free survival will be analyzed in the intent to treat population. For the primary analysis, in each stratum, a one sided logrank test stratified for pre-specified stratification factors will be used, and tested at the significance level of 0.10. The size of the treatment difference will be measured by the estimated hazard ratio and its 95% confidence interval.

The progression free survival rates will be estimated as a function of time by the Kaplan-Meier method. Overall survival will be analyzed in the intent to treat population. The overall survival rates will be estimated as a function of time by the Kaplan-Meier method. Time to progression rates will be estimated as a function of time by the Kaplan-Meier method in the intent to treat population. Response rates at 3 and 6 months, progression-free rates at 3 and 6 months will be analyzed by descriptive techniques (intent to treat analysis).

The occurrence of adverse events will be analyzed in the safety population, by descriptive techniques. For each type of adverse event, the worst grade observed across the whole therapy will be tabulated by treatment arm, and the percentages of grade 2+ and grade 3+ cases will be provided. For events occurring in more than 10% of the cases at a grade 2+, the cumulative incidence will be computed as a function of time for each grade, by treatment arm, considering discontinuation of therapy for reasons other than an adverse event as a competing risk.

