### Statistical considerations

#### Statistical hypothesis – Sample size calculation

The primary endpoint is progression-free survival (PFS) according to RECIST 1.1 guidelines and with central radiological review. The sample size is calculated on the basis of the primary endpoint. The study consists of 4 parallel phase II trials in 4 sub-populations defined by histology: liposarcoma, leiomyosarcoma, synovial sarcoma and other sarcomas. Recent literature data suggest that PFS with placebo is about 1.6 months [14]. The expected PFS with regorafenib is 4.6 months. Statistical assumptions for the 3 most frequent histological subtypes (liposarcoma, leiomyosarcoma and other sarcomas) are: PFS0 = 1.6, PFS1 = 4.6, alpha = 0.1 (one-sided) and power (1-β) = 0.95, the sample size is 50 patients per stratum (30 expected events). For the Synovial sarcoma stratum, based on its low prevalence and in order to not delay significantly the duration of the study, lower power is considered acceptable and only 25 patients will randomized in this cohort (Alpha = 0.10, Beta = 0.20, 16 events and 25 patients).

At the end, the total number of patients is calculated as follows: (50x3) + 25 = 176 (+10% of non-valuable patients: 192)

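### The 80% and 95% power figures belong to an unstratified log-rank test; at 16 and 30 events the stratified primary test gives roughly 70% and 91–93%

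*Protocol article*

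**What the plan says.** Under Statistical hypothesis – Sample size calculation, the three larger cohorts are planned with "PFS0 = 1.6, PFS1 = 4.6, alpha = 0.1 (one-sided) and power (1-β) = 0.95", for which "the sample size is 50 patients per stratum (30 expected events"). The synovial cohort is planned with "Alpha = 0.10, Beta = 0.20, 16 events and 25 patients". That section mentions no stratification.

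Under Randomization and stratification: "Within the 4 strata, stratification factors will be: prior exposure to pazopanib (yes/no) and countries". The abstract names three countries, so a cohort can have up to 2 × 3 = 6 cells. Allocation is 1:1 in permuted blocks.

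Under Statistical analysis, the primary test in each cohort is "a one sided logrank test stratified for pre-specified stratification factors will be used, and tested at the significance level of 0.10".

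No section says that the analysis takes place at the 16th or 30th event. Study endpoints only censors patients who are event-free when the analysis is done.

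**The concern.** Power, event count, test and stratification factors are all fixed in this article, and they do not fit together. In a stratified log-rank test, an event contributes only if both arms still have patients at risk in its cell. With 25 patients in up to six cells there are about 25/6 ≈ 4 patients and 16/6 ≈ 2.7 events per cell, so many late events carry no information. The sample size formula makes no allowance for this. It is also somewhat optimistic for so large an effect with so few events.

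Each cohort is analysed on its own, so its stated power governs how its negative result is read. The protocol accepts a 20% miss rate for synovial sarcoma as a deliberate concession to rarity. If the analysis were done at 16 events, the risk actually accepted would be larger than the one disclosed.

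**Working it through.** **Inputs from the protocol article.** Median PFS 1.6 and 4.6 months; one-sided alpha 0.10; 1:1 allocation; 50 patients and 30 events, or 25 patients and 16 events. Randomization and stratification gives 26 synovial patients; the difference does not affect the result.

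**1. Reproducing the plan's figures (unstratified Schoenfeld).** HR = 1.6/4.6 = 0.348; ln HR = −1.056; (ln HR)² = 1.1153.
- 95% power: 4 × (1.2816 + 1.6449)² / 1.1153 = 30.7 events
- 80% power: 4 × (1.2816 + 0.8416)² / 1.1153 = 16.2 events
- Power at 30 events: Φ(√30/2 × 1.056 − 1.2816) = Φ(1.61) = 0.946
- Power at 16 events: Φ(√16/2 × 1.056 − 1.2816) = Φ(0.83) = 0.797

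The printed figures are therefore reproduced, for an unstratified test.

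**2. Sensitivity to the formula (Freedman).** [(1 + 0.348)/(1 − 0.348)]² = 4.27. This gives 4.27 × 8.56 = 36.6 and 4.27 × 4.51 = 19.3, or 37 and 20 events. Power at 30 and 16 events is 0.914 and 0.743. Choosing Schoenfeld is legitimate, but the two formulas differ noticeably here.

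**3. Simulating the stated test at the stated event counts.** Exponential PFS, permuted blocks within pazopanib × country cells, cut at the stated event. Assumed, because the article does not give them: pazopanib share (30% as the main value), country shares, block size (4) and the shape of accrual.

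| Cohort | Stated | Unstratified, simulated | Stratified, simulated |
|---|---|---|---|
| Synovial, 16 events | 0.80 | 0.75–0.80 | 0.68–0.75 |
| 50 patients, 30 events | 0.95 | 0.93–0.95 | 0.91–0.93 |

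Individual settings vary around these ranges:
- Synovial, entry over 18 months, 30% pazopanib, blocks of 2: 0.705 with two countries (85/15) and 0.677 with three (70/20/10).
- Synovial, three countries and simultaneous entry: 0.71–0.74. Three equal countries with staggered entry is the low end, at about 0.64–0.66.
- 50-patient cohorts, three countries and staggered entry: 0.89–0.91.
- Scan-visit ties, blocks of 2 and a prognostic effect of pazopanib (HR 2) made no material difference.
- Type I error of the stratified test at 25 patients and 16 events: 0.108.

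No setting that used both factors reached the stated power at the stated events.

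**4. Rough cross-check.** With staggered entry, about a quarter to a third of synovial events were uninformative. Removing a quarter leaves 12: Φ(√12/2 × 1.056 − 1.2816) = Φ(0.55) ≈ 0.71. Removing a third leaves 10.7: Φ(0.44) ≈ 0.67. This agrees with the simulation in size, but does not apportion the gap. In the simulations, up to about 5 points come from small-sample error of the formula and the rest from sparse cells.

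**5. If the analysis waits for full enrolment.** The Accrual section dates the start to June 2013. It reports two cohorts closed by 1 May 2014 (about 11 months) and expects recruitment to end between December 2014 and February 2015 (about 18–20 months). Taking 18 months' accrual for synovial and 11 for the others, then 1–3 months' further follow-up:
- Synovial: about 20–22 events, stratified power 0.75–0.83.
- 50-patient cohorts: about 36–41 events, stratified power 0.95–0.97.

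**6. Events that bring the stratified test to the stated power.** In the 50-patient cohorts, 37 events give 0.94–0.96. With 25 synovial patients, 22 events give 0.82 (two countries, 85/15) or 0.79 (three, 70/20/10); all 25 give 0.83 or 0.79.

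**The case against.** The strongest reply is that the low power depends on a cut-off the article never sets. For the larger cohorts 30 is only an expected number of events, and nothing says the analysis is triggered at 16 or 30. On the documented accrual, a cut at the 16th synovial event would tend to fall before recruitment ends. Step 5 shows that full enrolment with modest follow-up largely restores the stated power. This stands. A reader might infer that the true miss rate in synovial sarcoma is 30–35%; the document does not support that as a property of the trial, only as a property of an analysis made at 16 events.

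Three further points stand in part:
- A reader might call the sample size arithmetic wrong. It is not: 0.946 and 0.797 match the printed powers. The fault is that the formula and the test differ.
- The lowest simulated values need three countries of similar size. The Accrual section reports sites in France and Austria only, with 152 of 192 patients enrolled and two cohorts closed, so four cells may be nearer the truth than six for those two.
- The protocol openly accepts lower power in the synovial cohort. It does so at a stated 80%, however, and 16 events do not provide that with the specified test.

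What the reply does not remove is the printed pairing itself: events and power are stated together, and the specified primary test does not deliver them together.

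**Conclusion.** The pairings of 16 events with 80% and 30 events with 95% are wrong for the primary test as specified. At those counts the stratified test has about 68–75% power in the synovial cohort, a shortfall of about 5–12 points, and about 91–93% in the larger cohorts, a shortfall of about 2–4 points. The first is material and the second modest. The direction held in every setting with both factors. The exact size rests on assumed country shares, pazopanib share and accrual, and some three-country settings fall below these ranges.

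The finding concerns power at the stated event counts. It does not show that the trial as run is underpowered, because the article leaves the time of analysis open and a plausible later analysis comes close to the stated power.

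**What to change.** In Statistical hypothesis – Sample size calculation, do one of the following:

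1. Keep 16 and 30 events and restate the power for the stratified test: about 70% for synovial and about 91–92% for the other three, with the assumed country and pazopanib shares shown.
2. Keep 80% and 95% and tie the analysis to the events or minimum follow-up that deliver them: about 37 events in each 50-patient cohort, and about 22 or more among the 25–26 synovial patients under the full stratification. With three countries, even that only just approaches 80%, and the text should say so.

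Either way, say that the printed event counts came from an unstratified calculation. No patients are added. Option 1 costs wording only. Option 2 costs a readout a few months later than a cut at 16 or 30 events; for 37 events, one simulation moved the cut from 6.9 to 8.9 months after first enrolment, under assumed accrual.

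Dropping country from the synovial primary test while keeping it in the randomisation would recover some power. It is a debatable trade-off, because the Methodological discussion chose both factors to address heterogeneous prior management. It is optional and not part of the required change.

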**Table 1 Tab1:** **Study procedures and flow-chart**

	Screening 14 days	d1, d30, d60, d90, d120	After the 4^th^month, every 3 months until tolerance or progession
Physical exam	X	X	X
Safety	X	X	X
Availbility of tumour sample	X		
Thoracic and abdominopelvic CT-Scann	X	X	X
Echocardio or MUGA	X		X
Hematology INR TCA	X	X	X
Biochemistry (1)	X	X	X
Urine Dipstick	X	X	X
Serum sample for TR programm		X	

(1) Serum creatinine, Glomerular filtration rate (Cockroff and Gault), AST, ALT, Bilirubin, Alkaline phosphatases, Amylase and lipase, CPK.

The patients will be randomly allocated to one of the treatment described above.Regorafenib: 4 tablets, once daily, 3 weeks on/1 week off

+ Best Supportive Care

OrPlacebo: 4 tablets, once daily, 3 weeks on/1 week off

+ Best Supportive Care

until progression or unacceptable toxicity in both arms.

Best supportive care includes any method to preserve the comfort and dignity of the patients and excludes any disease-specific anti-neoplastic agent.

Details on dose-adaptations, prohibited concomitant medications and the study flow-chart could be obtained by request to the corresponding author.

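### Whole-therapy worst-grade percentages are not adjusted for the longer observation expected on regorafenib, and the planned cumulative incidence corrects this only in part

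*Protocol article*

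**What the plan says.** Under Statistical analysis, the protocol article fixes the safety summary itself. It is descriptive and uses the safety population: "The occurrence of adverse events will be analyzed in the safety population, by descriptive techniques". The table for every event type is set out as follows: "the worst grade observed across the whole therapy will be tabulated by treatment arm, and the percentages of grade 2+ and grade 3+ cases will" also appear. Event types that exceed 10% at grade 2+ get a further analysis: "the cumulative incidence will be computed as a function of time for each grade, by treatment arm". Early stopping enters that analysis by "considering discontinuation of therapy for reasons other than an adverse event as a competing risk".

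Three other places bear on this:
- The treatment description after Table 1 continues therapy in both arms until progression or unacceptable toxicity.
- The overview of the study design counts a 30 (±7) day safety follow-up as part of the treatment period.
- The sample size section assumes "PFS0 = 1.6, PFS1 = 4.6, alpha = 0.1 (one-sided) and power (1-β) = 0.95" for the three larger strata.

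**The concern.** The time during which an adverse event can be counted depends on when the patient progresses, and the trial is designed on the expectation that regorafenib delays progression. A percentage of patients ever affected, with no denominator of time, will then tend to be higher in the arm that stays on therapy longer, even for events the drug does not cause.

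Background events matter here. In the two phase III trials summarised under Prior experience with regorafenib, fatigue was reported in 28.1% and 27.3% of placebo patients, and anorexia in 15.4% and 7.6%. Toxicity is a listed secondary endpoint, the table is laid out by arm against placebo, and the results may support a phase III decision. Readers will compare the columns.

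**Working it through.** **Inputs.** Median PFS 1.6 and 4.6 months (sample size section). Assessments at months 1, 2, 3 and 4, then every 3 months (Table 1). Safety window of 1 month (overview of the study design). Assumptions of this check: exponential PFS; therapy ends at the assessment that detects progression; follow-up ends at month 13 or 25; the event hazard h is constant and equal in both arms.

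**The plan's own figure.** HR = 1.6/4.6 = 0.348. Events by Schoenfeld's formula, 1:1, one-sided alpha 0.10, power 0.95: 4 × (1.2816 + 1.6449)² / (ln 0.348)² = 34.26/1.115 = 30.7, so 31. The plan states 30, which gives power 0.946. The synovial stratum at power 0.80 needs 17; 16 are stated, which gives 0.797. The medians used below are therefore the ones behind the design. The article gives no adverse event rate to reproduce.

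**Time on therapy.** A patient is still treated after visit v with probability 2^(−v/median). Summing probability × interval length gives a mean of 3.1 months on placebo and 6.6 to 7.6 on regorafenib, a ratio of 2.2 to 2.5. If therapy stopped at the moment of progression (continuous form), the means would be median/ln 2 = 2.31 and 6.64 months, ratio 2.9.

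**Crude whole-therapy incidence, no drug effect.** Sum over intervals of 2^(−prev/median) × exp(−h·prev) × (1 − exp(−h·length)), where prev is the start of the interval. The last column lets each patient remain at risk for one month after stopping.

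| h per month | Placebo | Regorafenib | Ratio | Ratio with 30-day window |
|---|---|---|---|---|
| 0.02 | 5.8% | 12.0–13.4% | 2.1–2.3 | 1.8–2.0 |
| 0.05 | 13.5% | 26.3–28.4% | 1.9–2.1 | 1.7–1.8 |
| 0.10 | 24.1% | 43.3–45.1% | 1.8–1.9 | 1.55–1.6 |

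The continuous form, h/(h + μ) with μ = ln 2/median (0.433 and 0.151), gives ratios of 2.66, 2.41 and 2.13. With the window they are 2.14, 1.94 and 1.72.

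**Planned cumulative incidence, no drug effect.** With discontinuation as a competing risk, the continuous form is h/(h + μ) × (1 − exp(−(h + μ)t)). At h = 0.10:

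| Month | Placebo | Regorafenib | Ratio |
|---|---|---|---|
| 1 | 7.8% | 8.8% | 1.14 |
| 4 | 16.5% | 25.3% | 1.53 |
| 12 | 18.7% | 37.9% | 2.03 |
| Plateau | 18.8% | 39.9% | 2.13 |

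The plateau is the crude proportion. In the visit-based form the arms are identical at month 1, and the ratio is about 1.35 at month 4.

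**Rate per patient-month.** Under the same assumptions, first events divided by event-free time at risk estimates h in each arm, so the ratio is 1.0.

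**The case against.** **The analysis is descriptive.** No between-arm safety test is planned, and worst grade over therapy is a legitimate description of toxicity as experienced. Both are true. No error rate is at stake, which limits the weight of the point. It does not change how columns laid out by arm will be read.

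**A time-resolved analysis is already planned.** This stands in part. A reader might infer that the crude table is the only summary by arm, or that the arms must differ by construction and the results cannot be read. The article does not support that: for common events the curves are usable early, with a ratio of 1.0 to 1.14 at month 1. What remains uncovered is every event type at or below the 10% threshold, and the later part of every curve.

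**Exposure-adjusted rates may be in an analysis plan that is not shown.** Possibly. The point here concerns what the article itself fixes as the safety summary, not what it leaves out.

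**The hazards are assumed, and a constant hazard may fit poorly.** This also stands. In the GIST trial (median PFS 0.9 vs 4.8 months), placebo fatigue was 27.3%. The equal-hazard continuous model would predict about 67% on regorafenib, or 57% with a 30-day window; 38.6% was observed. Those were events judged drug-related, so the comparison is imperfect, but it suggests that such events come early rather than steadily. Stopping for toxicity is also ignored here, and it would shorten regorafenib exposure.

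**The visit schedule.** It is tempting to add that the change from monthly to 3-monthly checks after month 4 widens the difference between arms. It does not. The schedule is the same in both arms, and the article offers the full flow-chart on request. It nowhere says that events are recorded only at these visits. Any lost capture would fall mainly on regorafenib and shrink the excess: if 67% or 33% of events after month 4 were captured (assumed; h = 0.10, continuous form), the ratio of 2.13 would fall to 2.02 or 1.83.

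**Conclusion.** The point holds in a limited form. The worst-grade percentages are not adjusted for time at risk. With the trial's own medians and a steady, equal hazard of 0.02 to 0.10 per month, they would be about 1.8 to 2.3 times higher on regorafenib without any added risk, or about 1.5 to 2.0 times with the 30-day window. The size rests on the assumed hazard, exponential PFS and stopping at the detecting scan. It would be smaller for higher hazards, and small for events concentrated in month 1. The cumulative incidence is a partial remedy, limited by its threshold and by its convergence to the crude proportion.

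Restricting the cumulative incidence to d1–d120 might look like an unbiased comparison, but it still carries a ratio of about 1.35 (visit-based) to 1.5–1.6 (continuous). The primary PFS analysis is not affected. The change is worth making because it is cheap, not because the planned tables are invalid.

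**What to change.** Keep the worst-grade table and the cumulative incidence curves. Add the following for every adverse event type, at grade 2+ and at grade 3+, without the 10% threshold:

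1. The first-event rate per patient-month by arm, with a confidence interval. Time at risk runs over blinded therapy plus the 30-day safety window. It should end at the first open-label regorafenib dose if that comes sooner, so that open-label time is not counted as placebo time.
2. The incidence by d30, by arm.

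State that the whole-therapy percentages describe toxicity burden and are not the between-arm contrast.

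The cost is a few sentences in the analysis section and a few tables; no new visits, data or patients are needed. The downside is that a person-time rate summarises well only when the hazard is roughly constant. It should be read together with the d30 incidence, which shows early events.

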#### Pre-planned sensitivity or exploratory analyses

A sensitivity analysis of progression free survival will be conducted in the per protocol population, if more than 5% of the randomized patients are excluded from the analysis.

Data from patients treated with regorafenib after “cross-over” will be analyzed (activity – PFS, Time to progression, best objective response, PFR3 and PFR6, OS- and tolerance) with classical descriptive methods.

### Translational research (TR) program

TR analyses will be done at the Institute of Pathology Medical University Graz in Austria.

The analysis consists of two parts:The first part “integrated TR” includes the central review of histopathology on paraffin embedded tumor blocks. The central confirmation of histopathological diagnoses is mandatory to include patients into the outlined study. Immunohistochemistry (IHC) and molecular analysis (FISH and RT-PCR) will be performed to confirm the diagnosis, if not previously performed in reference centers.2.The second part “exploratory TR” component will further characterize the nature of the genetic change by exploring the mutational status of the tumor samples using the Ion AmpliSeq™ Cancer Panel, Life Technologies Corporation. In addition it is planned to construct a tissue-micro arrays (TMA) from FFPE material to allow a large-scale evaluation of molecular aberrations and downstream effects on pathway activation.

The key objectives of this translational research are:Identification and characterization of biomarkers.Exploration of specific molecular changes that can potentially be used as predictive markers of response to regorafinib.Better definition of the patient population most sensitive to regorafinib.

Formalin fixed, paraffin embedded (FFPE) or fresh frozen tissue samples collected either from the primary tumor or from metastatic sites, or both will be analyzed.

Immunohistochemistry and molecular analysis [fluorescence in situ hybridisation (FISH) and reverse transcriptase polymerase chain reaction (RT-PCR)], will be performed to investigate chromosomal aberrations characteristic for specific sarcoma subtypes (e.g. Synovial Sarcoma SYT-SSX1 and SYTSSX2). Genetic changes will be investigated by exploring the mutational status of the tumor samples using the Ion AmpliSeq™ Cancer Panel V2 SNP analysis (47 genes, 790 hotspots), Life Technologies Corporation. In addition to this screening approach the full coding sequence of VEGFR1-3, TIE2, PDGFRB, FGFR1, KIT, RET1 and RAF will be explored. Submitted paraffin blocks will be used to construct a tissue microarray (TMA). This TMA will allow exploring potential predictive or prognostic factors for treatment response and eventually validation of newly discovered genes as diagnostic and therapeutic targets. The panel of IHC antibodies will strongly depend on the results of third generation sequencing. Formalin fixed paraffin embedded (FFPE) tumor blocks will be collected for all patients (this is mandatory for study participation). Blocks must be accompanied by electronic information on histopathology reports and, if applicable, by written reports on previously performed molecular analysis of the tumor. Slides are not acceptable. FFPE blocks may be from primary or metastatic sites. Residual FFPE material will be used for the planed exploratory translational research. FFPE materials must be from tissue samples taken prior to any treatment with regorafinib. Tumor blocks will be return to the patient center after analysis.

